## Abstract

A randomized crossover trial was designed to investigate the influence of muscle activation and strength on functional stability/control of the knee joint, to determine whether bilateral imbalances still occur six months after successful anterior cruciate ligament reconstruction (ACLR), and to analyze whether the use of orthotic devices changes the activity onset of these muscles. Furthermore, conclusions on the feedforward and feedback mechanisms are highlighted. Therefore, twenty-eight patients will take part in a modified Back in Action (BIA) test battery at an average of six months after a primary unilateral ACLR, which used an autologous ipsilateral semitendinosus tendon graft. This includes double-leg and single-leg stability tests, double-leg and single-leg countermovement jumps, double-leg and single-leg drop jumps, a speedy jump test, and a quick feet test. During the tests, gluteus medius and semitendinosus muscle activity are analyzed using surface electromyography (sEMG). Motion analysis is conducted using Microsoft Azure DK and 3D force plates. The tests are performed while wearing knee rigid orthosis, soft brace, and with no aid, in random order. Additionally, the range of hip and knee motion and hip abductor muscle strength under isometric conditions are measured. Furthermore, patient-rated outcomes will be assessed.

## 1. Introduction

The incidence of anterior cruciate ligament (ACL) tears has been reported as 68.6 per 100,000 cases per year [1], with a re-rupture rate of 1–11% after primary ACL reconstruction (ACLR) [2]. Long-term functional deficits are common in re-ruptures, e.g., chronic knee instability, meniscus tears, and cartilage damage [3,4,5]. In the long term, 50% of patients develop osteoarthritis after an ACL tear [6]. In addition, a failed ACLR is related to a rapid increase in cartilage degeneration [7]. Furthermore, ACL tears are associated with muscle atrophy, leading to a loss of functionality and stability of the knee [8]. Moreover, there is evidence that only about 50% of post-ACLR patients regain their preinjury athletic level [9]. In the worst case, this leads to the end of an athlete’s career [2]. Finally, it should also be considered that athletes with ACL tears have long rehabilitation periods and have to bear significant psychological burdens [10], which can highly influence their quality of life [11].

Multimodal programs are already established and focus on strength, flexibility, proprioception, and balance training. In addition, feedback training, understanding of biomechanics, and correct landing patterns are becoming increasingly important in the rehabilitation process [3,12]. Nevertheless, return to sport (RTS) programs show limited prospective value in terms of reinjuries [13]. Furthermore, there are no gold standard criteria for a safe RTS after ACLR [14]. Meanwhile, studies have shown that in addition to assessing quantitative criteria during the rehabilitation process, it is also essential to examine qualitative criteria such as dynamic knee valgus (DKV) [15], which increases during jump landing and thus increases the risk of an ACL injury [16]. In summary, this is the rationale for further investigation to identify the barriers and factors to successful rehabilitation and to bring athletes back to their preinjury sporting performance.

Less than ten years ago, the Back in Action (BIA) test battery, a standardized tool for deciding whether a patient is ready for RTS after an ACLR was developed and published [17]. The test battery consists of a double-leg stability test, a single-leg stability test, a double-leg countermovement jump (CMJ), single-leg CMJ, a plyometric jump test consisting of three plyometric jumps, a speedy jump test, and a quick feet test [17]. When analyzing the results, gender, patient age, and leg dominance are considered, providing an overview of the patient’s complete functional knee performance [17]. Studies have demonstrated that the BIA test battery is superior in showing side-to-side differences compared to other RTS test batteries [18], e.g., the standard hop and strength tests [19]. Therefore, introducing BIA in the decision-making process for a proper RTS is necessary to assess functional recovery and dynamic knee stability [19].

Knee orthotic devices are often recommended and used after ACLR. However, it is neither proven if there is a mechanical advantage of using them nor which orthotic device has the most effective influence on body balance and coordination and, thus, the function of the knee joint [20]. In a recently published pilot study that the present research team conducted on young participants without a history of knee problems, it was shown that rigid orthoses and soft braces have neither a positive nor a negative influence on the BIA test battery results [21]. It was concluded that in healthy subjects, knee coordination and knee function are not influenced by using orthotic devices. The risk of injury or accident in sports does not seem to increase further, as no influence on knee coordination has been demonstrated. It remains unclear whether there is a preventive effect or minimization for the risk of injury and a resulting advantage for patients with ACLR. A systematic review showed that the influence of prophylactic knee bracing in American football does not seem to reduce the incidence of knee injuries [22]. As it is currently not conclusively proven whether there are any advantages or disadvantages using orthotic devices, this study will assess the aspect of athletic performance during the BIA test battery.

Soft or rigid orthotic devices may support feedback strategies through skin contact and thus increase the subjective feeling of safety, resulting in a willingness to perform. In addition, braces and orthoses provide patients with security (even if only psychologically) but are not mechanically proven. The immediate clinical relevance is that orthotic devices either positively or negatively influence the tested performance on RTS or not.

For sporting performance and benefits to be taken from orthotic devices, the feedforward and feedback strategies model is becoming increasingly important. Feedforward and feedback control are generally explained as mechanisms to restore homeostasis in an organism [23]. Therefore, feedback can be described as a response to a sensory detection (e.g., unstable joint position during landing maneuvers), and using previous experience (e.g., jumping exercises) to make an appropriate modification (e.g., adjustment of knee position). On the other hand, feedforward control describes the preparatory action that occurs before an event. Experiences are initially brought into pre-activation. When repeatedly performing a jump, the athlete can better estimate how much force must be used to optimize the performance. Restoration of functional stability in the knee joint occurs through unconscious dynamic control in preparation for and in response to the movement [23]. Therefore feedforward, as an anticipatory strategy, and feedback, as an action occurring in response to the sensory detection, are helpful strategies to achieve the movement goal and optimize training in rehabilitation [23]. Feedforward is mainly based on experience with an expected task. A good reproduction of real effects occurs when no specific preparation for a complex task is carried out, because the more complex the task, the less feedforward mechanisms can take effect [23,24].

Surface electromyography (sEMG), is an objective method to analyze muscular activation and coordination patterns during the execution of movements [25]. Cross et al. examined the EMG activity of the semitendinosus and gracilis muscles six months after they were harvested for ACLR and found no significant decrease in EMG activity [26]. However, after harvesting the semitendinosus graft for ACLR, regeneration of the muscle takes up to one year [27]. Therefore, it would be interesting to evaluate a possible difference in muscle activation between the limbs under sporting conditions six months after surgery.

Furthermore, the role of gluteus muscles on DKV is not fully clarified [28]. Due to the controversial discussion a possible correlation between muscle activation patterns and DKV will be investigated.

Motion tracking systems are a common instrument to track postural control [29]. The Microsoft Azure Kinect DK can be used to analyze the knee axis during some of the BIA test battery components. The methods provide the therapist and the patient with objective feedback on the development of performance in rehabilitation [30,31].

Furthermore, device-based strength measurements are considered the gold standard for assessing muscle function [32]. Therefore, they are useful tools for evaluating strength status during rehabilitation, especially when used in interventional designs [33]. A recent study showed that weak hip muscles in hip abduction, extension, and external rotation impact DKV in collegiate female athletes in single-leg tasks [34].

To the best of our knowledge, there have been no studies conducted to investigate the following aspects using the specifically designed BIA test battery, yet:The influence of rigid orthoses and soft braces on the performance of the knee jointThe activation of the gluteus medius and semitendinosus muscles and the associated influence on the cumulative DKV during landing maneuversConclusions on feedforward and feedback mechanisms during the test battery

### Objectives and Hypothesis

In this study, we will perform the functional and biomechanical assessment of patients six months (+/−1 month) after unilateral primary ACLR using an autologous hamstring tendon graft with a test battery, using either a knee rigid orthosis, knee soft brace (medi^®^ company, Medi Bayreuth, Germany) or no aid.

Our aim is to investigate the influence of muscle activation on functional stability/control of the knee joint to determine whether bilateral imbalances still occur six months after successful ACLR and to analyze whether the use of a brace or orthosis changes the activity onset of these muscles.

Furthermore, conclusions on the feedforward and feedback mechanisms are also highlighted.

In the event of significant lateral limb differences in muscle activity and DKV emergence persisting six months after ACLR, the results give reason to explore strategies to optimize the rehabilitation process, implement adapted exercises to reduce lateral limb differences, and improve the outcome of knee functionality to reduce the risk of a reinjury.

In addition, conclusions will be drawn about the influence and possible effectiveness of using orthotic devices and the associated benefits for patients. Based on the results, coaches, athletes, and medical staff need to have (no) concerns that individual use of supports/orthoses will affect athletic performance and RTS test results, which may help athletes who like to continue wearing aids for psychological reasons to decide on their usefulness. Based on the research questions, it can be hypothesized:

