**Hypothesis** **1:**
*Soft braces or rigid orthoses improve functional performance during the modified BIA test battery.*

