### 2.2. Participants

Participants will be recruited at the Sporthopaedicum, Center for Orthopaedics, Sports Medicine and Orthopaedic Surgery in Berlin (Germany) and the University Hospital of Brandenburg, Center for Orthopaedics and Traumatology (Germany). Suitable patients are selected via a file review and invited for a surveillance test. The test battery is performed six months (+/−1 month) postoperatively to observe the greatest possible difference while reducing the risk of reinjury to a minimum.

The studied cohort of 28 patients consists of female and male patients. Only a large impact on performance is internally valid for estimating whether braces or orthoses should be worn as they are used to reduce adverse events. For this reason, a potential cut off for wearing braces or orthoses was set at a large estimated effect. A large effect for the investigated three degrees of freedom, with an acceptable alpha error of 0.05 and a 1-beta error of 0.9, results in a required total sample size of 27 when using an ANOVA: fixed effects, special, main effects, and interactions model. To catch up one possible drop out, which is not expected, a sample size of 28 is included.

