## 4. Data Analysis and Planned Statistical Analysis

All data are presented in a descriptive manner, including anthropometric data and absolute measured values. Side-to-side differences are calculated for all SL tests, using the limb symmetry index (LSI). Therefore, absolute values of the ACL-reconstructed leg are divided by the values of the unaffected leg and multiplied by 100. For the stability, quick feet and speedy tests LSI is calculated by dividing the measured value of the unaffected leg by the value of the ACL-reconstructed leg and multiplied by 100 according to the calculation done in the study by Herbst et al. [17].

Power is quantified in the sagittal plane and defined through force and velocity. This parameter is directly extracted from the force plate data and reported as extracted. It is assessed for jumping during loading phase and total jump height. Power is based on peak power calculations for the lower extremity, which is defined in newton for maximal applied force during contraction. Additionally, it will be interpreted in the context of recent LSI-papers.

Descriptive quantitative data are calculated as the mean ± standard deviation. The Kolmogorov-Smirnov test is used to test the normality assumption. To compare the variances across the means of the three groups we use ANOVA repeated measures. Wilcoxon and Friedman-Test are used as well to calculate between-group differences.

All statistical analyses are performed using SPSS (IBM SPSS Statistics, New York, NY, USA). The significance level for all statistical tests is set a priori to 0.05. A post-hoc power analysis is conducted when significant effects are found.

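### A non-significant device comparison in 28 patients can support at most *no large effect shown*, not the foreseen message of no concerns; post-hoc power after significance adds nothing

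*Protocol article*

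**What the plan says.** Under Objectives and Hypothesis, the article describes the practical message that the results are to carry: "coaches, athletes, and medical staff need to have (no) concerns that individual use of supports/orthoses will affect athletic performance and RTS test results". The bracketed word leaves both directions open, and no effect size is attached to either.

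Hypothesis 1 is one of improvement: "Soft braces or rigid orthoses improve functional performance during the modified BIA test battery".

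Section 2.2 (Participants) sets the target: "Only a large impact on performance is internally valid for estimating whether braces or orthoses should be worn", and "a potential cut off for wearing braces or orthoses was set at a large estimated effect". The sample size is calculated "with an acceptable alpha error of 0.05 and a 1-beta error of 0.9", which gives 27 patients, plus one for a possible dropout. No numerical value is given for the large effect.

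Section 4 compares the three conditions by repeated-measures ANOVA, Wilcoxon and Friedman tests. It adds: "The significance level for all statistical tests is set a priori to 0.05" and "A post-hoc power analysis is conducted when significant effects are found".

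**The concern.** One of the two foreseen messages is a negative one: devices do not affect performance or return-to-sport test results. The article's only decision tool is a test of difference. Followed as written, it would rest that message on a failure to reject, which shows a lack of evidence for a difference and does not bound the difference.

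The effect used for sizing does not close the gap. It was chosen as a threshold above which wearing a device would be worthwhile. It was not chosen as the largest change in performance that could be ignored. A moderate effect in either direction could go undetected and still be passed on as no cause for concern to athletes who are weighing up whether to keep wearing an aid.

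The post-hoc power sentence is a separate, smaller fault: it commits the team to a calculation that tells the reader nothing new.

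**Working it through.** **Inputs.** From the article: n = 28 (27 plus one), three conditions per patient, alpha 0.05, planning power 0.90, "A large effect for the investigated three degrees of freedom". Assumed, because the article gives no figures: the value of f for *large*, the within-patient correlation rho between conditions, sphericity, and effects in units of the SD of the paired difference.

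**1. The plan's own figure.** For a fixed-effects ANOVA, lambda = f² × N, with df1 = 3 and df2 = N minus the number of groups (three used here).
- f = 0.80, N = 27: lambda = 0.64 × 27 = 17.28, power 0.910. N = 26 gives 0.896. So 27 is reproduced.
- f = 0.40: N = 93 is needed, and 28 patients have about 34% power.

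The stated 27 therefore follows from the stated model if *large* means f = 0.80, and not if it means f = 0.40.

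**2. Power of the analysis actually planned.** For repeated-measures ANOVA with three conditions, lambda = f² × n × 3 / (1 − rho), with df = 2 and 54 at n = 28.

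| f (assumed) | rho = 0 | rho = 0.3 | rho = 0.5 |
|---|---|---|---|
| 0.40 | 90% | 98% | 99.7% |
| 0.25 | 50% | 66% | 81% |
| 0.10 | 11% | 14% | 19% |

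Example: f = 0.40, rho = 0 gives lambda = 0.16 × 28 × 3 = 13.44 and power 0.901. A null result therefore speaks against a large effect, but for moderate or small effects it says little unless the correlation is high.

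**3. One device-versus-no-aid contrast.** The 95% interval half-width in SD of the paired differences is t(27; 0.975)/√28 = 2.052/5.292 = 0.388. An estimate just short of significance is near 0.388 SD, so its interval reaches almost 2 × 0.388 = 0.78 SD in one direction.

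Power of the paired t-test (non-centrality d × √28, two-sided 0.05):

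| True difference (SD) | Power | Missed |
|---|---|---|
| 0.2 | 17% | 83% |
| 0.3 | 33% | 67% |
| 0.4 | 53% | 47% |
| 0.5 | 72% | 28% |

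The difference detectable with 90% power is 0.64 SD.

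**4. Post-hoc power at the observed effect.** Setting the non-centrality equal to the observed t makes power a function of p alone. For a paired t-test with 27 df:
- p = 0.05 (t = 2.052): 51%
- p = 0.01 (t = 2.771): 76%
- p = 0.001 (t = 3.690): 94%

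For the omnibus F test with 2 and 54 df, taking lambda as 2 × F, the values are about 58%, 79% and 94%. The figures differ, but p determines them in both cases.

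**The case against.** **The article never says that non-significance means no concern.** This is correct. The bracketed wording sits in a motivating paragraph and depends on the results, and the discussion keeps improvement and deterioration both open. A reader might infer a fixed decision rule, but the text contains none. What stands is narrower: the article announces a possible negative message and describes no analysis other than difference tests to support it.

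**The trial is openly sized for a large effect.** This also stands in part. A reader might conclude that a null result would have no valid basis at all. The calculation does not support that: under the planned repeated-measures ANOVA, 28 patients have at least 90% power at an assumed f = 0.40, so *no large effect* is a fair reading. But the foreseen message is not limited to large effects, and the threshold was set for deciding to wear a device, not for ruling out a change in performance.

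**Margins and intervals may be in a document not shown.** Their absence from a condensed article is not the fault raised here, and difference tests suit a hypothesis of improvement. The message and the post-hoc power rule, however, are both stated in the article.

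**Post-hoc power is not offered as protection for null results.** Agreed. A reader might link the two, but the sentence applies only after significance and cannot affect a null conclusion. It also does not say *observed* power; power at a pre-stated effect size would not be fixed by p.

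**Conclusion.** The concern holds in limited form. As the article stands, a non-significant device comparison would justify *no large effect shown* and nothing broader. The interval for a single contrast is about ±0.39 SD of the paired differences, and a true difference of 0.3 SD would be missed about 67% of the time, one of 0.4 SD about 47%. These figures assume 28 complete patients, approximately normal paired differences and a two-sided 0.05 test without multiplicity adjustment. The statement that a large effect would probably be detected assumes f = 0.40 and sphericity.

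The post-hoc power sentence is uninformative if, as is usual, power is computed at the observed effect. Data collection is unaffected; what changes is what the trial may conclude.

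**What to change.** 1. Delete the post-hoc power sentence in section 4.
2. Report each device-versus-no-aid contrast with its 95% confidence interval.
3. Reword the paragraph under Objectives and Hypothesis so that a non-significant result is reported as *no large effect shown*, with the interval stating which effects remain possible.
4. Allow a no-concern statement only if the interval excludes differences that the investigators judged relevant and stated before data collection. Otherwise call the result inconclusive.

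The relevant difference must come from subject-matter judgement, not from what 28 patients can deliver. For example, a margin of 0.6 SD has about 85% power at a true difference of zero (two one-sided tests at 0.05 each, by simulation). Yet it would declare equivalence about 46% of the time at a true 0.3 SD and 27% at 0.4 SD, so convenient power is no reason to choose it.

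The cost is a few sentences, plus a decision on which performance outcome the statement refers to and what difference on it matters. No extra patients or procedures are needed. The drawback is that some null results will have to be reported as inconclusive.

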**Hypothesis** **1:**
*Soft braces or rigid orthoses improve functional performance during the modified BIA test battery.*

**Hypothesis** **2:**
*Muscle activity of the gluteus medius and semitendinosus muscles is impaired in the ACL-reconstructed leg during the modified BIA test battery.*

**Hypothesis** **3:**
*Impairment of gluteus medius and semitendinosus muscle function is related to lower performance in the operated limb in the modified BIA test battery.*

**Hypothesis** **4:**
*An impairment of gluteus medius strength and semitendinosus muscle activation correlates with DKV and pelvic drop emergence during the modified BIA test battery.*

## 2. Methods

Ethical approval is currently under consideration in the county medical chamber as an extension to a previously approved ethical application. The processing number is 22-TEMP897788-BO.

The assessment will be conducted in the Rehathleticum, a functional diagnostic physiotherapy center in Berlin (Germany).

A signed informed consent form and the confirmation of personal data protection will be obtained. Participants can withdraw from the study at any time without giving a reason. All data is anonymized by assigning a patient number so that a later assignment of personal data is only possible via the Sporthopaedicum in Berlin and the University Hospital of Brandenburg, Center for Orthopaedics and Traumatology. All measures are taken to protect the privacy of the subjects and the confidentiality of personal data.

